#### (3) Participant timeline

Study will commence with the eligibility screen for participants. Once eligibility is confirmed, the patient will sign an informed consent and be allocated to one of nine active rTMS group. Clinical assessments and functional magnetic resonance imaging (fMRI) scan will be performed at baseline (W0), termination of 20 rTMS sessions (W5) and the follow-up (W17). In the any phase of the study procedure, we will record the number and reasons for any participants who will be excluded or any who will decline consent or withdraw from the study. The SPIRIT schedule and the flowchart of the study are presented in Fig 1.

**Fig 1 pone.0271283.g001:**
[figure not shown]
The schedule of the trial.

#### (4) Sample size

Because no previous orthogonally designed study provides a significant difference of MoCA or MMSE scores for rTMS treatment to PSCI, which would allow us to accurately estimate the adequate sample size for this trial, we decided to recruit 45 PSCI patients who will be randomly divided into nine groups and three subgroups based on orthogonal design (5 patients per group, 15 patients per stimulating site subgroup), in consideration of the research grant, the recruitment feasibility and the recommended sample size in neuroimaging research (medians:14.5) [17].

#### (5) Recruitment

This trial aims to recruit 45 in- or outpatients with PSCI in the West China Hospital of Sichuan University who are recommended by the rehabilitation physicians, therapists, or any other medical practitioners and willing to receive rTMS treatment. Once the oral consent to take part in the study is confirmed, written and verbal information about the study aim and procedures is provided to all the volunteer participants. There are no biological specimens collecting for storage and anticipated harm for the participants throughout the study. All the personal information and any other data about the potential or enrolled patients will be traceable in the medical records and available from the corresponding author on request in order to protect confidentiality. After the written informed consents are obtained from the eligibility-screened participants, the study will commence with the baseline assessment and then the randomized allocation.

#### (6) Randomization and blinding

The random numbers sequence is generated using SPSS software in computer and all eligible patients were equal assigned to one of nine active rTMS treatment group based on four rTMS parameters. The random allocation and detailed rTMS protocol are only known by the rTMS physiotherapists and blinded to physicians, patients and other researchers (such as outcome assessors, data analysts). The rTMS physiotherapists are not involved in any other study work such as patient recruitment, randomization, allocation, outcome assessment and data analysis.

### 2. Interventions

#### (1) rTMS protocol

The rTMS treatments were delivered by a magnetic simulator (YRD CCY-I, YIRUIDE medical equipment co., LTD, Wuhan, China) with a figure-8 coil. The rTMS protocol was designed as nine combinations of four parameters at three different levels in each parameter: stimulating site (the dorsolateral prefrontal cortex, DLPFC, Brodmann areas 9 and 46; the inferior frontal gyrus, IFG, Brodmann areas 44 and 45; the temporo-parietal cortex, TPC, Brodmann areas 39 and 40), frequency (5Hz, 10Hz, 20Hz), intensity (90%, 100%, 110% of the resting motion threshold, RMT) and pulse number (1000, 1500, 2000), the detailed information are showed in Tables 1 and 2. The aforementioned rTMS parameters and different levels were predetermined based on the previous studies involving in rTMS treatment to cognition impairment duo to various neurological and psychological diseases. Once the PSCI patients were recruited, they were randomly allocated into one of nine active rTMS groups, a total of 20 sessions (four weeks, five consecutive daily sessions and two days of rest per week) active rTMS treatments with different parameters combination will be administered by two therapists with more than 5 work experience at the neuromodulating center of the rehabilitation medicine department, West China Hospital, Sichuan University. In order to improve the patient’s adherence to the intervention protocols, once every rTMS session was completed, a predesigned treatment record card should be filled and signed by the rTMS therapists and the patients or their authorized persons and ultimately returned to the study researchers.

**Table 1 pone.0271283.t001:** The orthogonal experimental factors and levels of rTMS.

Level	Experimental factor			
	A (Site)	B (Frequency, Hz)	C (Intensity, %RMT)	D (Pulse)
1	DLPFC	5	90	1000
2	IFG	10	100	1500
3	TPC	20	110	2000

Note: DLPFC: Dorsolateral prefrontal cortex; IFG: Inferior frontal gyrus; RMT: Resting motor threshold; rTMS: Repetitive transcranial magnetic stimulation; TPC: Temporoparietal cortex

**Table 2 pone.0271283.t002:** The orthogonal array L9(34).

Groups	Site (A)	Frequency (B)	Intensity (C)	Pulse (D)	rTMS protocols	Sample Size
1	TPC	5 Hz	100%RMT	1500	A_3_B_1_C_2_D_2_	5
2	IFG	20 Hz	100%RMT	1000	A_2_B_3_C_2_D_1_	5
3	IFG	10 Hz	90%RMT	1500	A_2_B_2_C_1_D_2_	5
4	TPC	10 Hz	110%RMT	1000	A_3_B_2_C_3_D_1_	5
5	DLPFC	5 Hz	90%RMT	1000	A_1_B_1_C_1_D_1_	5
6	IFG	5 Hz	110%RMT	2000	A_2_B_1_C_3_D_3_	5
7	DLPFC	10 Hz	100%RMT	2000	A_1_B_2_C_2_D_3_	5
8	TPC	20 Hz	90%RMT	2000	A_3_B_3_C_1_D_3_	5
9	DLPFC	20 Hz	110%RMT	1500	A_1_B_3_C_3_D_2_	5

Note: A_1_: DLPFC; A_2_: IFG; A_3_: TPC; B_1_: 5Hz; B_2_: 10Hz; B_3_: 20Hz; C_1_: 90%RMT; C_2_: 100%RMT; C_3_: 110%RMT; D_1_: 1000; D_2_: 1500; D_3_: 2000; DLPFC: Dorsolateral prefrontal cortex; IFG: Inferior frontal gyrus; RMT: Resting motor threshold; rTMS: Repetitive transcranial magnetic stimulation; TPC: Temporoparietal cortex

The detailed information of parameters and grouping were as following:

Group 1: TPC; 5 Hz; 100%RMT; 1500 pulses (10s × 20 trains, 10s interval)Group 2: IFG; 20 Hz; 90%RMT; 1500 pulses (3s × 25 trains, 20s interval)Group 3: IFG; 10 Hz; 100%RMT; 1000 pulses (4s × 25 trains, 20s interval)Group 4: TPC; 10 Hz; 90%RMT; 2000 pulses (8s × 25 trains, 20s interval)Group 5: DLPFC; 5 Hz; 90%RMT; 1000 pulses (8s × 25 trains, 20s interval)Group 6: IFG; 5 Hz; 110%RMT; 2000 pulses (20s × 20 trains, 20s interval)Group 7: DLPFC; 10Hz; 110%RMT; 1500 pulses (6s × 25 trains, 20s interval)Group 8: TPC; 20 Hz; 110%RMT; 1000 pulses (2s × 25trains, 20s interval)Group 9: DLPFC; 20Hz; 100%RMT; 2000 pulses (5s × 20 trains, 20s interval)

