### 4. Statistical analyses

The data of MoCA-BJ, TMT, MBI, LIADL and SS-QOL were shown as mean ± standard deviation (SD) and analyzed by the range analysis and one-way analysis of variance (ANOVA), which was used the SPSS 22.0 software (IBM, Armonk, NY, USA, 2020). The range analysis was used to determine the influence of each parameter at a specific level on the effect indicator and obtain the optimum combination of rTMS parameters. The one-way ANOVA was used to determine the statistical significance in nine different parameters’ combination of rTMS. P < 0.05 was considered significant.

For ALFF and FC maps, paired T-test will be used for intra-group comparison and one-way ANOVA analysis will be used for inter-group comparison in the three stimulating site subgroups. Then multiple comparison correction will be performed using Gaussian random field theory (GRF) with voxel *p* < 0.005, cluster *p* < 0.05. The Pearson correlation analyses were used to calculate the correlations between the changes in ALFF and FC with the clinical symptom scores at baseline and the end of the rTMS treatment (*p* < 0.05).

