### 6. Trial status

This trial was registered on the website of Chinese Clinical Trial Registry (Registration number: ChiCTR2100049625; https://www.chictr.org.cn/). At the writing of this paper, we are recruiting subjects. The study began in December 2021 and planned to complete in December 2023.

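### Group 1's printed train settings deliver 1000 pulses per session, not the 1500 stated in the same line and in Table 2

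*Protocol article*

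**What the plan says.** The design has four factors at three levels each. One of them is "pulse number (1000, 1500, 2000", coded in the note to Table 2 as "D_1_: 1000; D_2_: 1500; D_3_: 2000". Table 2 gives group 1 as TPC, 5 Hz, 100% RMT, 1500 pulses, with pulse code D2.

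The list below Table 2 adds the train settings. For group 1 it reads "Group 1: TPC; 5 Hz; 100%RMT; 1500 pulses (10s × 20 trains, 10s interval". Two other lines, for comparison, are "Group 2: IFG; 20 Hz; 90%RMT; 1500 pulses (3s × 25 trains, 20s interval" and "Group 5: DLPFC; 5 Hz; 90%RMT; 1000 pulses (8s × 25 trains, 20s interval".

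Under 4. Statistical analyses, the factor levels enter through the range analysis: "The range analysis was used to determine the influence of each parameter at a specific level on the effect indicator". Under (6) Randomization and blinding, "The random allocation and detailed rTMS protocol are only known by the rTMS physiotherapists", and data analysts are among those blinded. Under 6. Trial status, the article says "At the writing of this paper, we are recruiting subjects".

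**The concern.** Frequency, train length and number of trains together fix the number of pulses. For group 1 they give a different level of a study factor from the one the group is assigned to. The train settings are also the part of the line that would be set up for delivery.

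If they were delivered as printed, group 1 would be a 1000-pulse cell analysed as a 1500-pulse cell. The range analysis compares simple level means and relies on each level of one factor meeting each level of every other factor equally often. With group 1 at 1000 pulses that balance fails between pulse number and each of the other three factors, so part of any pulse effect would appear as an effect of site, frequency or intensity. An analysis by group label would not reveal this, and patients may already have been treated.

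**Working it through.** **Inputs.** Frequency, train length, number of trains and stated pulses come from the list under (1) rTMS protocol. The Table 2 pulses come from Table 2.

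**Step 1. Pulses per session = frequency (Hz) × train length (s) × number of trains.**

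| Group | Calculation | Result | List | Table 2 |
|---|---|---|---|---|
| 1 | 5 × 10 × 20 | **1000** | **1500** | **1500** |
| 2 | 20 × 3 × 25 | 1500 | 1500 | 1000 |
| 3 | 10 × 4 × 25 | 1000 | 1000 | 1500 |
| 4 | 10 × 8 × 25 | 2000 | 2000 | 1000 |
| 5 | 5 × 8 × 25 | 1000 | 1000 | 1000 |
| 6 | 5 × 20 × 20 | 2000 | 2000 | 2000 |
| 7 | 10 × 6 × 25 | 1500 | 1500 | 2000 |
| 8 | 20 × 2 × 25 | 1000 | 1000 | 2000 |
| 9 | 20 × 5 × 20 | 2000 | 2000 | 1500 |

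The formula reproduces the list for groups 2 to 9, so it is the article's own convention, and group 1 is the only line that fails. Counting the 10 s interval as stimulation does not help: 5 × 20 × 20 = 2000.

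The list and Table 2 also disagree on intensity and pulse number for groups 2, 3, 4, 7, 8 and 9. That is a separate conflict. For group 1 they agree with each other, and the train settings fit neither.

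**Step 2. Dose, if delivered as printed.** The shortfall is 500/1500 = 33% per session. Over 20 sessions it is 20,000 pulses against 30,000. Group 1 has 5 of the 45 patients, or 11%.

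**Step 3. Balance.** As labelled, the list and Table 2 are both valid L9 arrays: all six factor pairs show 9 of 9 level combinations. With group 1 at 1000 pulses, either array drops to 8 of 9 for site–pulse, frequency–pulse and intensity–pulse. The pulse levels then occur in 4, 2 and 3 groups. A main-effects model still has full rank (9).

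**Step 4. Leakage into the range analysis.** Let d be the true 1500-minus-1000 effect. The document gives no value, so d is an assumption. Each level mean averages three groups, so the labelled TPC, 5 Hz, 100% RMT and 1500-pulse means each fall by d/3. With no true effect of site, frequency or intensity, each of these three factors shows a false range of d/3: 0.17, 0.33 or 0.67 points for d = 0.5, 1 or 2, and none for d = 0.

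As an example, assume pulse effects of 0, 1 and 2 for 1000, 1500 and 2000 pulses, with the other cells as listed:

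- Site (DLPFC, IFG, TPC): 1, 1, 0.67
- Frequency (5, 10, 20 Hz): 0.67, 1, 1
- Intensity (90, 100, 110% RMT): 1, 0.67, 1
- Pulse as labelled (1000, 1500, 2000): 0, 0.67, 2

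Here the pulse range stays 2.0 and 2000 stays best. That depends on the assumed shape: if 1500 were truly best, but by less than d/3 over 2000, the labelled means would favour 2000.

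**Step 5. Size against noise.** With 15 patients per level, the expected range of three level means by chance alone was simulated with 1,000,000 sets.

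| Assumed SD (points) | Chance alone | With d = 1 |
|---|---|---|
| 2 | 0.87 | 0.93 |
| 3 | 1.31 | 1.35 |
| 4 | 1.75 | 1.78 |

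**Step 6. Cost of coding as delivered.** These are contrast variances in units of SD², from a main-effects model with 5 patients per group and all five group 1 patients affected.

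| Contrast | As designed | As delivered |
|---|---|---|
| 1000 vs 1500 | 0.133 | 0.300 |
| 1500 vs 2000 | 0.133 | 0.233 |
| 1000 vs 2000 | 0.133 | 0.133 |
| Any involving TPC, 5 Hz or 100% RMT | 0.133 | 0.167 |
| Other site, frequency and intensity contrasts | 0.133 | 0.133 |

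**The case against.** The intended dose is hardly in doubt. The list label, the Table 2 pulse column and the Table 2 code all give 1500 for group 1, and both arrays are balanced only with that value. A slip in one field, such as 20 for 30 trains or 10 s for 15 s, is the simplest reading. The 10 s interval, against 20 s in every other group, points the same way. Nothing in the document shows that 1000 pulses were delivered, so every analytic consequence is conditional.

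The one-way ANOVA on the clinical outcomes compares the nine combinations as groups. Its F and P values are the same whether group 1 is called 1000 or 1500; for these outcomes only the range analysis uses the factor level. The error is also traceable: a signed treatment card is completed at every session and returned to the researchers, although the article does not say whether it records pulse counts.

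All of this stands, and it limits the weight of the point. It does not remove the error. The line remains wrong for anyone delivering or replicating group 1 from it, and the range analysis is the method that selects the optimum combination.

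**Conclusion.** The error is certain: the group 1 settings give 1000 pulses against 1500 stated. It should be fixed, because it concerns the dose of a study factor in a trial that is already recruiting.

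Whether it had any effect is unknown. If it is a misprint, delivery and analysis are sound. If it was delivered as printed, the bias in the site, frequency and intensity ranges is d/3. Under the assumed d = 1 and SD of 2 to 4 points, this raises the expected range by only 0.03 to 0.06. That smallness rests on assumed values of d and SD, since the document gives neither. The conclusion does not depend on which of the two arrays is correct.

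**What to change.** Correct the group 1 train settings so that they give 1500 pulses: 15 s × 20, 12 s × 25 or 10 s × 30 trains all do so at 5 Hz. State whether the 10 s interval is intended. Do this together with reconciling Table 2 and the list for the six groups on which they differ, because the group 1 line does not settle which array is right.

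Have someone outside the blinded team check treatment cards or device logs for group 1 patients already treated. If any received 1000 pulses, add a sensitivity analysis that codes pulse number as delivered in a main-effects model, and accept the loss of precision shown in step 6.

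The cost is one line of text and a record check for at most five patients. The conflict between Table 2 and the list is a larger correction in its own right.

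### Table 2 and the group list exchange intensity and pulse number in six of nine groups, and group 1's train recipe delivers 1000 pulses, not 1500

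*Protocol article*

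**What the plan says.** Methods 2(1) (rTMS protocol) sets out four factors at three levels: site (A), frequency (B), intensity (C: 90, 100, 110 %RMT) and pulse number (D: 1000, 1500, 2000). Nine groups of five patients are assigned by an L9 orthogonal array.

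The groups are specified in two places. For Tables 1 and 2 the text says "the detailed information are showed in Tables 1 and 2". After Table 2 comes a list of the same nine groups, introduced by "The detailed information of parameters and grouping were as following". The list adds train length, number of trains and interval. Examples are:

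- "Group 1: TPC; 5 Hz; 100%RMT; 1500 pulses (10s × 20 trains, 10s interval")
- "Group 2: IFG; 20 Hz; 90%RMT; 1500 pulses (3s × 25 trains, 20s interval")
- "Group 4: TPC; 10 Hz; 90%RMT; 2000 pulses (8s × 25 trains, 20s interval")
- "Group 8: TPC; 20 Hz; 110%RMT; 1000 pulses (2s × 25trains, 20s interval")

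Table 2 gives group 2 as 100%RMT with 1000 pulses, group 4 as 110%RMT with 1000 pulses and group 8 as 90%RMT with 2000 pulses. Neither version is said to take precedence.

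Section 4 (Statistical analyses) uses range analysis to judge each parameter level and to "obtain the optimum combination of rTMS parameters".

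**The concern.** The trial exists to find the best parameter combination. Range analysis does this by averaging the groups at each level of each factor and taking the best level, so the result depends wholly on which groups are assigned to which level. With two incompatible assignments in print, patients could be treated under one and analysed under the other. Intensity and pulse-number effects would then be reported under each other's name.

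Little in the design would expose such a swap. Section 1(6) (Randomization and blinding) says that only the physiotherapists know the detailed rTMS settings, and that they take no part in data analysis.

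Group 1 raises a second question: whether its printed train recipe delivers the pulse number that both versions claim.

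**Working it through.** **Inputs.** Table 2 cells and level codes, and the list's labels and train recipes, all from Methods 2(1). Site and frequency agree in all nine groups, so only intensity and pulses are compared. Recipe pulses = frequency (Hz) × train length (s) × number of trains.

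| Group | Table 2: %RMT / pulses | List: %RMT / pulses | Recipe pulses |
|---|---|---|---|
| 1 | 100 / 1500 | 100 / 1500 | 5×10×20 = **1000** |
| 2 | 100 / 1000 | 90 / 1500 | 20×3×25 = 1500 |
| 3 | 90 / 1500 | 100 / 1000 | 10×4×25 = 1000 |
| 4 | 110 / 1000 | 90 / 2000 | 10×8×25 = 2000 |
| 5 | 90 / 1000 | 90 / 1000 | 5×8×25 = 1000 |
| 6 | 110 / 2000 | 110 / 2000 | 5×20×20 = 2000 |
| 7 | 100 / 2000 | 110 / 1500 | 10×6×25 = 1500 |
| 8 | 90 / 2000 | 110 / 1000 | 20×2×25 = 1000 |
| 9 | 110 / 1500 | 100 / 2000 | 20×5×20 = 2000 |

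**1. Pattern.** Groups 2, 3, 4, 7, 8 and 9 differ on both factors: 6 of 9 groups, 6 × 5 = 30 of 45 patients. In level codes, every list row is its Table 2 row with C and D exchanged (group 2: C2D1 becomes C1D2). Groups 1, 5 and 6 agree only because they are C2D2, C1D1 and C3D3.

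**2. Text-extraction error?** No. Table 2's level codes repeat its own cells. The list's recipes reproduce the list's pulse counts in groups 2 to 9 and contradict Table 2's in all six discordant groups.

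**3. Can a design check tell the versions apart?** No. As labelled, both are valid L9 arrays: all six factor pairs show 9 of 9 distinct level combinations. Four three-level factors use 4 × 2 = 8 degrees of freedom, which is all there are between nine groups. Either coding therefore fits the nine group means exactly, and lack of fit cannot reveal a swap.

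**4. Effect of a mismatch.** Assume the list is delivered, Table 2 is coded, intensity truly adds 0/1/2 points at 90/100/110 %RMT, pulse number has no effect, and there is no noise. The group means for groups 1 to 9 are 1, 0, 1, 0, 0, 2, 2, 2, 1. Coded by Table 2:

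- Intensity: 90% (groups 3, 5, 8) = (1+0+2)/3 = 1; 100% (1, 2, 7) = (1+0+2)/3 = 1; 110% (4, 6, 9) = (0+2+1)/3 = 1. Range 0.
- Pulses: 1000 (2, 4, 5) = 0; 1500 (1, 3, 9) = 1; 2000 (6, 7, 8) = 2. Range 2.

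The whole intensity effect is credited to pulse number. More generally, the best C and D level numbers are exchanged. The chosen optimum is unchanged only if they coincide (C1D1, C2D2, C3D3), which is 3 of 9 possible pairs. In the other 6, both parameters are wrong.

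**5. Group 1, if its printed recipe is delivered.** Using recipe pulses throughout:

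- 1000/1500/2000 pulses go to 4/2/3 groups (20/10/15 patients) instead of 3/3/3.
- Mean pulses are (1000+2000+1000)/3 = 1333 for TPC, (1000+1000+2000)/3 = 1333 for 5 Hz, and (1000+1000+2000)/3 = 1333 for 100%RMT. Every other level of those factors has 1500.
- Pulse number paired with site, frequency or intensity covers 8 of 9 combinations, so the array is no longer orthogonal.
- If group 1 is still coded as 1500 and the true 1000-to-1500 effect is e points, one of the three groups behind each of the TPC, 5 Hz, 100%RMT and 1500-pulse means is off by e. Each of those means shifts by e/3.

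**The case against.** The harm is conditional. If delivery and coding both follow the same version as labelled, the array is sound and the range analysis attributes effects correctly. Nothing in the article shows that they diverge, and a coding key may sit in a fuller document. The article also hints at the answer: only the list gives deliverable settings, and its recipes fit its own pulse counts in eight of nine groups. The likeliest reading is that the list is operational and that Table 2 has two columns exchanged. Group 1 may be a simple misprint; its 10 s interval is also unlike the 20 s used in every other group. The nine-group one-way ANOVA and the site-subgroup imaging comparisons do not use the C and D codes at all.

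All of that stands as a limit on consequence. It does not remove the contradiction. A condensed article may omit detail, but here it states two incompatible treatment assignments in one section, and no other part resolves them (the Discussion repeats the levels, not the groupings). If the list is operational, then Table 2, the formal statement of the array, is the version that is wrong, and it is the natural source for anyone coding the analysis.

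**Conclusion.** The concern holds. Six of nine groups (30 of 45 patients) have contradictory intensity and pulse settings. Counting group 1's recipe, which is a different kind of error, 7 of 9 groups (35 of 45) carry at least one conflicting setting. In groups 4 and 8 the two versions differ by 20 percentage points of RMT and by a factor of two in pulses.

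The contradiction and the group 1 shortfall follow directly from the printed values. The misattribution of effects rests on an assumed delivery/coding mismatch, and the 0-against-2 example is an illustration, not a forecast. The imbalance figures for group 1 rest on its recipe being delivered as printed. The intensity/pulse exchange leaves the site and frequency means, as labelled, unaffected; a group 1 shortfall would not. Because the optimum combination depends on this assignment, it needs to be settled before the range analysis.

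**What to change.** 1. State which array is intended and correct whichever of Table 2 or the list is wrong.
2. Correct group 1's recipe to give 1500 pulses at 5 Hz, for example 15 s × 20 trains or 10 s × 30 trains (5 × 300 s = 1500).
3. Recruitment was open when the article was written (section 6, Trial status), so verify the settings that each enrolled patient received. Methods 2(1) says that after every session "a predesigned treatment record card should be filled and signed by the rTMS therapists" and by the patient or an authorized person. If the cards do not hold settings, use therapist or device records.
4. Freeze one analysis-coding file that matches the delivered settings before the range analysis. If group 1 patients received 1000 pulses, code them as 1000 and report the loss of balance.

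The cost is one correction to the protocol (and to the allocation key, if it carries the same error), one corrected recipe, and a check of existing records. No extra patients are needed. If 1000 pulses are now being delivered, group 1 sessions lengthen by 20 × 5 s = 100 s with the first recipe, or by 10 × (10 s + 10 s interval) = 200 s with the second.

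### Group 1's delivery line gives 1000 pulses, not the 1500 stated, and train number varies outside the L9 array (20 in groups 1, 6 and 9; 25 in the other arms)

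*Protocol article*

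**What the plan says.** All references are to the protocol article. Methods 2(1) describes the intervention so: "The rTMS protocol was designed as nine combinations of four parameters at three different levels in each parameter". The four are site, frequency, intensity and pulse number. Below Table 2, a list gives each arm's train length, number of trains and interval:

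- "Group 1: TPC; 5 Hz; 100%RMT; 1500 pulses (10s × 20 trains, 10s interval"
- "Group 6: IFG; 5 Hz; 110%RMT; 2000 pulses (20s × 20 trains, 20s interval"
- "Group 9: DLPFC; 20Hz; 100%RMT; 2000 pulses (5s × 20 trains, 20s interval"
- "Group 4: TPC; 10 Hz; 90%RMT; 2000 pulses (8s × 25 trains, 20s interval"

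Groups 2, 3, 5, 7 and 8 also have 25 trains. The interval is 20 s in every arm except group 1.

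Methods 4 ranks the level means to name the best combination: "The range analysis was used to determine the influence of each parameter at a specific level on the effect indicator". Methods 6 gives the status: "At the writing of this paper, we are recruiting subjects".

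**The concern.** There are two problems in one list.

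- **Group 1's schedule does not deliver its stated pulses.** Pulse number is a ranked factor, and the range analysis compares plain level means. That is fair only if each level of one factor meets each level of the others once.
- **Train number differs between arms but is not a factor.** Four three-level factors use 4 × 2 = 8 degrees of freedom, and nine arms supply 8. Within an arm every patient is meant to receive the same number of trains, so no covariate added later can separate its effect. Any such effect falls on the means from which the optimum is read.

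**Working it through.** **Step 1. Reproduce the stated pulse numbers.** Pulses = Hz × seconds per train × trains.

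| Group | Hz × s × trains | Delivered | List states | Table 2 states |
|---|---|---|---|---|
| 1 | 5 × 10 × 20 | 1000 | 1500 | 1500 |
| 2 | 20 × 3 × 25 | 1500 | 1500 | 1000 |
| 3 | 10 × 4 × 25 | 1000 | 1000 | 1500 |
| 4 | 10 × 8 × 25 | 2000 | 2000 | 1000 |
| 5 | 5 × 8 × 25 | 1000 | 1000 | 1000 |
| 6 | 5 × 20 × 20 | 2000 | 2000 | 2000 |
| 7 | 10 × 6 × 25 | 1500 | 1500 | 2000 |
| 8 | 20 × 2 × 25 | 1000 | 1000 | 2000 |
| 9 | 20 × 5 × 20 | 2000 | 2000 | 1500 |

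Eight of nine agree with the list; group 1 does not. Against Table 2, only groups 5 and 6 agree.

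**Step 2. What group 1 does to the array.** If the line is followed, the arms at 1000/1500/2000 pulses number 4/2/3 instead of 3/3/3 (20/10/15 patients instead of 15/15/15). TPC, 5 Hz and 100% RMT then have no arm at 1500. This is the same under the list and Table 2.

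Let d be the true 1500-minus-1000 difference, with additive effects. If group 1 is still labelled 1500:

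- the observed difference between those levels has expectation 2d/3, because one of the three arms labelled 1500 received 1000;
- the TPC, 5 Hz and 100% RMT means are each off by d/3.

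If group 1 is coded as 1000, the main-effects model can still be fitted (rank 9 of 9 under either allocation), but it is no longer orthogonal. With 15 patients per level and outcome SD σ, the SE of a level difference in the balanced array is σ√(2/15) = 0.365σ. Undoing the factor 2/3 raises the SE of the 1500-minus-1000 difference to 1.5 × 0.365σ = 0.548σ.

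**Step 3. Where a train-number effect lands.** Let t be the effect of 20 rather than 25 trains, the same in every arm. The range added to a factor is t × (largest minus smallest count of 20-train arms per level)/3.

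| Case (list governs) | Site DLPFC/IFG/TPC | Frequency 5/10/20 | Intensity 90/100/110 | Pulses 1000/1500/2000 |
|---|---|---|---|---|
| As printed (groups 1, 6, 9) | 1/1/1, range 0 | 2/0/1, 2t/3 | 0/2/1, 2t/3 | 0/1/2, 2t/3 |
| Group 1 repaired to 25 trains | 1/1/0, t/3 | 1/0/1, t/3 | 0/1/1, t/3 | 0/0/2, 2t/3 |

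Keeping 10 s trains, group 1 would need 1500/(5 × 10) = 30 trains. If the effect is linear in train number, groups 6 and 9 then carry +t and group 1 −t. The ranges become 2t/3 for site, t/3 for frequency and intensity, and t for pulse number.

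**Step 4. If Table 2 governs.** Only group 6 is a confirmed 20-train arm. If every other arm used 25 trains, each factor would gain t/3. If Table 2's three 2000-pulse arms (groups 6, 7 and 8) all used 20, pulse number would gain t and the other factors 0. The documents do not say which.

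**Step 5. Scale.** A range of 2t/3 equals one SE (0.365σ) when t = 0.55σ, and t/3 does when t = 1.10σ. The documents give no value for t.

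**The case against.** The strongest case against is that frequency × train length × trains must equal the pulse number, so some delivery variable has to vary. Fixing the trains at 25 leaves train length running from 2 to 16 s, and its mean still differs by site and intensity. The protocol also chose four parameters knowing that rTMS has more, and nothing in it shows that 20 rather than 25 trains matters. All of this stands, and it keeps the train-number part small. It does not touch group 1, whose line is wrong under either allocation.

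A reader might infer more than the documents support:

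- **That train number is aliased with all four parameters.** As printed, 20 trains occur once per site, so site is untouched. Site is reached only if group 1 is repaired to another train number.
- **That the ranking is pushed toward 2000 pulses.** This needs a size and a sign for t, and neither is given. The ranking may not move at all.
- **That each factor gains t/3 under Table 2.** This assumes 25 trains in arms whose schedules under Table 2 are not given.
- **That group 4 shows 20 trains are unnecessary for 2000 pulses.** This holds only under the list; Table 2 gives group 4 1000 pulses.
- **That the 10 s interval in group 1 is a real difference in delivery.** It may be a misprint, and nothing here rests on it.

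**Conclusion.** Group 1's schedule is wrong as written: 1000 pulses against the 1500 that the list and Table 2 both state. If followed, it shrinks the apparent 1500-versus-1000 contrast to two thirds and shifts three other level means by a third of that contrast, assuming additive effects and five patients per arm. This needs correction.

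The varying train number is a real but lesser weakness. Under the list as printed it adds 2t/3 to the ranges of frequency, intensity and pulse number and 0 to site, assuming t is the same in every arm. Under Table 2 the pattern is undetermined. It deserves attention mainly because the list has to be amended anyway.

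**What to change.** 1. Correct group 1 to 12 s × 25 trains with a 20 s interval (5 × 12 × 25 = 1500) when the list is reconciled with Table 2.
2. In the same amendment, use 25 trains and a 20 s interval in the other arms where few patients have been treated. Train length is then pulses/(25 × Hz), a whole number of seconds in every arm. Under the list, group 6 becomes 16 s and group 9 becomes 4 s, with the rest unchanged. Under Table 2, groups 1 to 9 become 12, 2, 6, 4, 8, 16, 8, 4 and 3 s. An arm that is mostly treated keeps its schedule, and the aliasing is reported.
3. For patients already treated, establish the delivered schedule. Methods 2(1) provides a source: "a predesigned treatment record card should be filled and signed by the rTMS therapists". If the card lacks train length, train number and interval, add these fields. Analyse group 1 patients at the pulse number delivered, with level means adjusted for the other three factors, because raw means are no longer balanced.
4. State as a limitation that level differences may partly reflect train number and train length.

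**Cost.** If the list governs, this is a short amendment and new stimulator presets for three arms (15 of 45 patients). Because recruitment is under way, arms of five may mix two schedules and must be flagged. Under the list, train length narrows from 2–20 s to 2–16 s. Its mean by site (DLPFC, IFG, TPC) goes from 6.3, 9.0, 6.7 s to 6.0, 7.7, 7.3 s. By intensity (90, 100, 110%) it goes from 6.3, 6.3, 9.3 s to 6.3, 6.7, 8.0 s. The aliasing is reduced, not removed.
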